### Other outcomes of interest

Social support and network:Personal recovery list and the Network and Support questionnaire. Those two self-developed questionnaires assess the patients’ perspective of social support and network.Relatives Evaluation scale (Betrokkenen Evaluatie Schaal (BES) in Dutch): relatives’ perspective support will be assessed using a short version of this questionnaire, existing of 22 items [47].Self-Efficacy:The Mental Health Confidence Scale (MHCS); 16-items questionnaire developed to measure self-efficacy in individuals diagnosed with mental disorders [48].Quality of life:Short Form health survey (SF-12); a set of 12 items measure the quality-of-life [49].European Quality of Life-5 Dimensions (EQ-5D-5L); a 6-item self-report about quality of health [50, 51].Manchester Short Assessment of Quality of Life (MANSA); a 16-item self-report [52].Alcohol and substance use:Alcohol Use Disorder Identification Test (AUDIT); an 10-item self-report about the use of alcohol [53]Measurements in the Addictions for Triage and Evaluation (MATE-Interview) [54].Cost-effectiveness:EuroQol (EQ-5D-5L), 5-point scale used to measure quality of life [55].Trimbos Institute and Institute of Medical Technology Questionnaire for Costs Associated with Psychiatric Illness (TiC-P) [56] and PROductivity and DISease Questionnaire (PRODISQ), short version [57]. Those questionnaires volume health care consumption and productivity loss.Institute for Medical Technology Assessment (iMTA) Valuation of Informal Care Questionnaire (iVICQ); 11-item questionnaire volumes delivered informal care and support by relatives [58].Staging and profiling:The Staging and Profiling scale (S&P) is a self-developed measure assessed by health care professionals for the duration and the severity of the illness.

### Handling and storage of data and documents

Once the participating patient provides written informed consent, a unique project number will be allocated to each participant. The key of these project numbers will only be available to the principal investigators, the relevant data managers and research assistants. All (paper and digital) questionnaires and data will be stored and handled using this project number (de-identified). Study outcomes will be reported anonymously. Storage of data will be supervised by the principal investigator and complies with the Dutch Personal Data Protection Act.

### Data analysis

#### Sample size calculation

We expect a 33% reduction in hospitalisation days at 52 weeks post-treatment allocation in IHT compared to CAU. This translates into a reduction of 20 hospitalisation days: 40 days (SD = 40) for IHT compared to 60 days (SD = 55) for CAU. Given the fact that data on the number of hospitalisation days will be collected (with permission) from the EHR of the participating treatment centres, a low non-response rate is expected: we expect that up to 5% of the participants will actively withdraw during follow-up based on previous studies performed by our research group [24]. Based on these figures, a sample size calculation using R version 3.2.2 software and the power calculation package ‘pwr’ was performed for the inter-group difference in hospitalisation days at 52 weeks after treatment allocation. Alpha was set at 0.05 (2-sided), power was set at 0.80. In addition, to ensure that a loss of statistical power does not occur due to cross-over of randomly allocated participants, 5% will be added to the calculated sample size [59]. A 2:1 allocation ratio will be applied because for reasons of staff and facility capacity. Taking into account these parameters, we need to include a total of *n* = 230 patients. 153 of them need to be allocated to and provide informed consent for IHT, 77 need to be allocated to and provide informed consent for CAU.

#### Cost-effectiveness calculations

The economic evaluation will be conducted as a cost-utility analysis using quality adjusted life years (EQ-5D/QALYs) as a generic measure of health gains. We will use the EQ-5D tariffs from both the UK [60] and the Netherlands [61]. Health utilities based on the SF-12 will be calculated using the Brazier’s algorithm [62]. The primary endpoint will be 12 months post allocation for the cost-utility analysis. The cost-utility analysis will be conducted and reported in agreement with the Consolidated Health Economic Evaluation Reporting Standards (CHEERS). The trial’s follow-up measurements do not exceed the time horizon of one year and therefore neither costs nor effects will be discounted. Sensitivity analyses will be directed at uncertainty in the main cost drivers. We will consider five types of costs: (1) the costs of offering the intervention, (2) costs stemming from health care uptake (e.g. hospitalisation) including the costs of medication, (3) patients’ out-of- pocket costs, (4) costs stemming from productivity losses due to absenteeism and reduced efficiency while at work (if the patient holds a job) and 5) costs of informal care network. We will perform the cost-utility analysis from at least two perspectives: (1) Societal perspective, (2) healthcare provider perspective. Volumes of direct medical contacts will be collected using the TIC-P and PRODISQ-short version, using the EHR of the participating institutions, and using external data sources such as from CBS if possible. These different but overlapping sources will be used in order to assess the reliability of the data sources. Delivered informal care and support by relatives will be measured using the iVICQ-short version. Unit costs for delivered care will be obtained from most recent costing manuals for the societal perspective, and unit costs for the healthcare provider perspective will be obtained from the Dutch Health Care Authority (NZa) averaged costs. Data presented will include incremental cost-effectiveness ratio’s (incl. Gains in QALY), and cost effectiveness acceptability curves. Uncertainty around the reported parameters will be assessed using non-parametric bootstrapping.

Analyses will be performed according to the intention-to-treat principle, with missing data addressed using multiple imputations [63]. Incremental cost-effectiveness ratio (ICER) will be calculated as follows: ICER = (CI1-CI2)/(EI1-EI2), where Care are costs, E effects, and subscripts I1 and I2 refer to the two interventions (IHT and CAU). Confidence intervals around the ICER will be calculated using a non-parametric bootstrap approach: 1000 non-parametric bootstrapped samples will be extracted from each of the original datasets. For each of these bootstrapped samples, the incremental costs, incremental effects, and the ICER will be calculated. The resulting 1000 ICERs per dataset will be used for further calculations and will be plotted on a cost-effectiveness plane. Based on the distribution of the ICERs over the cost-effectiveness plane, cost-effectiveness acceptability curves (CEACs) will be drawn. The CEACs show the probability that IHT is more cost-effective than CAU, as a function of the willingness to pay (WTP) for one additional unit of effect (e.g. for one QALY gained). One-way sensitivity analyses directed at uncertainty in the main cost drivers will be performed to gauge the robustness of our findings across a range of likely values of those parameters.

### Statistical analysis

The primary analyses will be conducted according to the intention to treat principle. A per protocol/treatment completer analysis will also be conducted. Generalized Linear Mixed Models (GLMM) will be used to model the primary outcome measure (hospitalisation days after 12 months, (over-dispersed) Poisson distribution) and secondary outcome measures (distributions as appropriate). Psychiatrist and organisation (Arkin or GGZ inGeest) will be included as random factors in the model. Missing data will be addressed using multiple imputation. All analyses will be performed using Statistical Package for the Social Science (SPSS) version 23 or higher, and using R (and relevant packages) version 3.2.2 or higher.

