### Study procedure

#### Recruitment

Arkin and GGZ inGeest are the two largest mental health care organisations in Amsterdam, the Netherlands and provide in- and outpatient psychiatric care in Amsterdam for children and adults of all ages. The Psychiatric Emergency Service Amsterdam (PES) is a cooperation between these two organisations. Referrers to PES include general practitioners, other mental health professionals and the police. A professional of PES performs psychiatric assessments, prepares a treatment plan with the patient in cooperation with his family and other professionals, and provides care as described in the treatment plan. PES is available 24 h a day, 7 days a week. The IHT teams are part of PES.

In this study, participants are recruited via IHT teams and the in-patient facilities of Arkin and GGZ inGeest between 8.30 AM and 10.00 PM. During the night, between 10:00 PM and 8:30 AM, PES Amsterdam is functioning as a gatekeeper for Arkin and GGZ inGeest. During night hours patients assessed by this service will receive CAU, i.e. voluntary or involuntary psychiatric admission or community-based care, with support from PES if necessary. The next day, these patients will be screened to check if they meet the in/exclusion criteria for this study. If participants have been admitted to a psychiatric ward during the weekend, they will be screened for study participation the next working day.

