### Demographic variables

At baseline, participants complete questions concerning basic demographic details; those questions include age, gender, country of origin, parents or relative’s country of origin, domestic situation, education level, occupational status and income. Drug history will be requested from the pharmacy (with participant’s consent), while the use of mental health care in the year before allocation to this study will be collected from the EHR system. The use of other health care will be collected from the CBS data (with participant’s consent) and the TiC-P instrument.

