### Primary outcome measure

The number of hospitalisation days in the 52 weeks after randomisation is the primary outcome measure. This includes the duration of the initial admission at baseline, and any subsequent psychiatric admission during the 12 months follow-up period of the study. Data will be collected from the EHR system of both mental health care organisations.

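### The primary model, as described, names no patient-level baseline covariate although prior-year care is already extracted; prespecified adjustment would gain precision, and the start of the bed-day count needs one clarifying sentence.

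*Protocol article*

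**What the plan says.** **Model.** Under Statistical analysis, the protocol article says that "Generalized Linear Mixed Models (GLMM) will be used to model the primary outcome measure". It gives an over-dispersed Poisson distribution for hospitalisation days, makes psychiatrist and organisation random factors, and handles missing data by multiple imputation. It does not list the fixed effects; even the treatment term is implicit.

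**Available baseline data.** Under Demographic variables, "the use of mental health care in the year before allocation to this study will be collected from the EHR system". The primary outcome comes from the EHR of the same two organisations. Under Consent and mental competence, patients may agree to the use of existing data sources only.

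**Timing of randomisation.** Under Recruitment, "During night hours patients assessed by this service will receive CAU", which may mean admission or community-based care, and these patients are screened the next day. Patients admitted at a weekend are screened on the next working day. Screening and pre-randomisation happen in one step.

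**Outcome.** Under Primary outcome measure, the count covers the 52 weeks after randomisation. The next sentence adds: "This includes the duration of the initial admission at baseline".

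**The concern.** Assumed bed-day SDs are close to the means (40 on 40, 55 on 60), so the treatment difference will be estimated with wide uncertainty. A baseline variable that predicts bed days would narrow it at almost no cost. Prior-year care is a natural candidate: it comes from the outcome's own source, it should be available for patients who consent to existing data only, and it is fixed before allocation. Interview baselines lack that last property because they are collected only after consent, which follows randomisation. The section on pre-randomisation names no stratification factor, so nothing described in the design or the model addresses an imbalance in prior bed use or in who was already in hospital.

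The outcome wording raises a second, smaller matter. If a patient was admitted on Friday night and randomised on Monday, the full duration of the initial admission includes nights before randomisation. Neither arm can influence those nights, and they lie outside the stated window. Two people extracting the data could count them differently.

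**Working it through.** **1. Reproduce the planned sample size.** Inputs from Sample size calculation: "Alpha was set at 0.05 (2-sided), power was set at 0.80"; "40 days (SD = 40) for IHT compared to 60 days (SD = 55) for CAU"; "A 2:1 allocation ratio will be applied because for reasons of staff and facility capacity"; "we expect that up to 5% of the participants will actively withdraw during follow-up"; and a further 5% for cross-over.

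- Equal-weight pooled SD = sqrt((40² + 55²)/2) = 48.09; standardised difference = 20/48.09 = 0.416.
- CAU patients = (1.960 + 0.842)² × 48.09² × (1 + 1/2) / 20² = 68.1, so 69; IHT = 138; total 207.
- Inflation: 207/0.90 = 230.0; 207/0.95² = 229.4; 207 × 1.05/0.95 = 228.8.

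The stated 230 is reproduced with no covariate, so the planned power does not depend on adjustment.

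**2. Power without adjustment after 5% withdrawal.** 153 × 0.95 = 145 and 77 × 0.95 = 73.

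- With the pooled SD of 48.09: power 82.3%.
- With separate SDs: SE = sqrt(1600/145 + 3025/73) = 7.24; 20/7.24 = 2.76; power 78.8%.

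Whether power is above or below 80% depends on which SD formula is used.

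**3. Gain from adjustment.** The documents give no correlation between any baseline variable and bed days, so r is an assumption. In a linear model the residual variance is (1 − r²) times the unadjusted variance.

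| Assumed r | Variance multiplier | SE multiplier | 230 patients worth | Power at 145/73, pooled SD | Power at 145/73, separate SDs |
|---|---|---|---|---|---|
| 0 | 1.00 | 1.00 | 230 | 82.3% | 78.8% |
| 0.3 | 0.91 | 0.95 | 230/0.91 = 253 | 85.6% | 82.5% |
| 0.5 | 0.75 | 0.87 | 230/0.75 = 307 | 91.5% | 89.0% |

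Here r stands for the joint correlation of the adjusted covariates with the outcome. The planned model is an over-dispersed Poisson model with a log link, so these figures are a guide to scale and not exact.

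**4. Nights before randomisation.** Under the Recruitment timing, an overnight admission adds about one night and a weekend admission about two or three. Suppose, as an upper case, that every patient in both arms had three such nights counted. The expected means would become 43 and 63 instead of 40 and 60. The difference stays at 20 days, and the ratio moves from 40/60 = 0.667 to 43/63 = 0.683. Since only night and weekend admissions are affected, the true effect would be smaller.

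**The case against.** The strongest reply is that a condensed article is silent on covariates and does not exclude them. It lists no fixed effects at all, and covariate lists are commonly left to the analysis plan, which is not shown. That stands. A reader might infer that the primary analysis has been fixed as unadjusted; the text does not say so. What remains is that the article names the model's other terms and already collects a suitable covariate, so the recommendation is concrete.

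Other stronger readings also fail:

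- **That these are strong predictors, or the main driver of bed days.** No figure supports this. The one statement on what determines the length of the care phases, under Care as usual, points mostly to symptom severity, danger and social factors such as housing and support.
- **That both variables are already recorded.** This is documented only for prior-year care. Inpatient status at randomisation appears neither under Demographic variables nor in Table 1; it would be derived from EHR admission dates.
- **That night patients are often admitted.** No frequency is given.
- **That power is already below 80%.** This holds only with separate SDs, not with the pooled SD that reproduces 230.
- **That unstratified randomisation leaves a flaw.** Chance imbalance is covered by the confidence interval and does not invalidate the comparison.
- **That adjustment cures consent-related selection.** It can at most help with the measured part.

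On the outcome, it is fair to say that the opening phrase about the 52 weeks after randomisation governs the sentence that follows. That is the likely intention, but the second sentence refers to the duration of the initial admission without limiting it to that window.

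**Conclusion.** The point holds as a recommendation for efficiency. The model as described names no patient-level covariate, while prior-year care is collected from the EHR and fixed before allocation. Adjustment would lower variance by roughly 9% if r = 0.3 and 25% if r = 0.5. At 145/73 that is about 3 to 4 and 9 to 10 percentage points of power, whichever SD formula is used. If the covariates explain much less than this, the gain is small. These figures assume a linear model and an unknown correlation. Nothing here shows the planned analysis to be invalid or the sample size to be wrong.

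The outcome wording is a real but small ambiguity, probably of one to a few nights for the patients concerned, and should be reconciled.

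**What to change.** 1. Before outcome data are examined, prespecify as fixed covariates in the primary model log(1 + inpatient days in the year before allocation) and inpatient status at randomisation (yes/no, derived from EHR admission dates). Age and sex are optional additions.
2. Use only values fixed before randomisation. Leave out diagnosis unless it comes from the screening record, because the baseline classification in Table 1 may be recorded after consent and hence after randomisation.
3. Report the unadjusted estimate as support, and give model-based mean days per arm beside the adjusted rate ratio.
4. Under Primary outcome measure, state that only inpatient nights from randomisation to 52 weeks count. Earlier nights of the same admission then fall in the prior-year covariate and are not lost.

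The cost is a few sentences in the analysis and outcome sections and one derived variable. No new data collection is needed, provided the EHR extract includes admission dates. Prespecification matters because the trial is open label, and covariates chosen after results are known would be open to challenge.

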### Monitoring, quality assurance and approvals

The study will be conducted in accordance to Good Clinical Practice guidelines and the Helsinki declaration. It is possible that the research project will be audited. During an audit an independent researcher will evaluate whether the study is being or has been performed in compliance with the quality standards of the Good Clinical Practise guidelines. Ethical approval has been obtained from the Medical Ethical Committee (METc) of the Vrije Universiteit medical centre Amsterdam (METc VUmc). This committee have approved the protocol and all amendments. If applicable, future amendments will be sent to the METc VUmc. In addition, the research team will submit a summary of the progress of the manuscript to the METc VUmc and the funder Stichting tot Steun VCVGZ once a year. Information will be provided on the date of inclusion of the first subject, numbers of subjects included and numbers of subjects that have completed the trial, serious adverse events/ serious adverse reactions, other problems, and amendments.

## Discussion

The study presented in this protocol paper is among the first RCTs worldwide to test the (cost-) effectiveness of 6 weeks of IHT compared to CAU (in- and out-patient crisis care without IHT teams). Primary outcome is the number of inpatient days compared to CAU, 12 months after randomisation. Secondary outcomes include safety of the patient, psychiatric symptoms and treatment satisfaction of the patient, his relatives and the professional.

Due to convictions of professionals and patients, “patients heal better in their own environment”, partially supported by previous research (e.g. [15]), economic and political pressure, IHT has been developed and may be broadly implemented without strong research evidence. The results of this study may ultimately help provide an evidence base to support or challenge the further implementation of IHT.

The design of this study must be evaluated in the light of the following strengths and challenges. Major strengths of this study are the follow-up period of 12 months and the relatively large sample size of 230 psychiatric crisis care patients. A major challenge is to perform an RCT in the acute mental health care setting. This challenge has led us to adopt the Zelen double consent design. At first we have considered the preferred RCT design: first obtaining informed consent followed by randomisation. But after discussions with the IHT professionals this design seemed impossible to implement in this study for a number of reasons:Patients in this study are in the midst of a psychiatric crisis. Patients have severe psychiatric symptoms, sometimes accompanied with severe danger for themselves or their network. They often experience a very emotional phase in their lives and are often surrounded by emotionally exhausted relatives. In this situation it is in our opinion unethical to ask for informed consent if this would delay a patient’s treatment.If treatment allocation by randomisation would take place after informed consent, patients and relatives are confronted with the fact that allocation depends on the outcome of a chance event. This may negatively influence their confidence in the selected therapeutic approach – even though there is no indication that one is superior to the other.Some patients lack insight in their illness in the most acute phase of the psychiatric crisis and therefore refuse treatment and do not want to cooperate with treatment and a study that is conducted to measure its effect.One of the powerful elements of the IHT intervention, i.e. the immediate initiation of patient’s and his relatives’ motivation for home treatment, would be weakened if consent would have to be sought prior to the start of treatment.

The research group therefore concluded that the pre-randomised Zelen double design would be a better and more feasible study design than the traditional RCT with consent before randomisation. Under the Zelen design, patients are randomised before consent to participate has been sought; so called pre-randomisation. In the Zelen double consent design all patients of both groups, the experimental and control group, will be fully informed about all aspects of the trial, including both treatment conditions, as soon as possible. Treatment starts immediately as the patient is presented to the professionals, without potential delays due to research consent procedures.

In addition to this allocation challenge that has led us to adapt the Zelen design, a number of practical challenges may arise while performing this study. For example, professionals may be biased towards one of the treatment conditions – which may impact the patient and his/her support for the provided treatment modality. In order to prevent this from impacting our study, we have frequent meetings with care professionals in order to answer their questions, resolve any worries, and to keep them positively involved in the study. Another challenge is the timing of the assessment of patients’ mental competence to provide informed consent. In case of doubt regarding this mental competence by the treatment professionals or the researchers, we use a structured and validated instrument to assess mental competence, and take up to 4 weeks to reassess mental competence in case of initial non-competence.

The key importance of this study is that it will provide insight in the (cost-)effectiveness of IHT for patients in a psychiatric crisis. The outcome of this study will provide additional evidence to guide the process of further reducing the amount and duration of psychiatric hospitalisations if possible, without jeopardising the quality and safety of care for patients in or on the verge of a psychiatric crisis.

